#### Isokinetic muscular power and work test

The power of knee extensor and flexor muscles will be measured in a sitting position using isokinetic dynamometers (Genu3 Easytech, Florence, Italy). After warm-up exercises, patients perform 4 maximal concentric strokes at an angular speed of 90° per second (knee extension flexion; ROM, 90–0°). Isokinetic tests will be performed when patients have no pain or swelling with ROM more than 120° of flexion with full extension. To ensure maximal effort, 3 to 4 training sessions are allowed before performing the test.

#### Vertical jump test

The subject should, therefore, be instructed to jump as high as possible and land on the same spot. If the subject deviates too far from this point (a landing area/spot can be marked out), then the result should be disregarded and the jump repeated. Once the test configuration has been set up and the subject and assessor are ready, then the test will begin: the participants should walk into the take-off/landing area and, when instructed to by the assessor, jump as high as they can and land on the same spot. At the peak of their jump height, they should hit the vanes of the Vertec device to displace as many of them as possible. This should be repeated so that the athlete completes 3 jumps in total. This way, an average or best of the three jumps can be calculated. Jump height is determined by the difference between the participants’ standing reach height and the highest vane displaced. The results of the test are reported in terms of jump height (cm). To ensure a valid and reliable result, it is a good practice to take an average of the three jumps performed by the athlete. The following formula can be used to calculate the average jump height: Average jump height = (jump 1 + jump 2 + jump 3)/3. Alternatively, the best score (i.e., highest jump) out of the three jumps can also be used.

#### Yo-Yo intermittent recovery test

Once the configuration of the tests has been set up, test principal investigator/officials are positioned at both shuttle lines (cone B and C), and participants are ready, then the test will begin. Participants begin the test from cone B. When instructed by the audio player, they must run towards cone C (this must be reached before the following beep signal) and immediately return to cone B before the next signal. Once cone B is reached, participants then have a 10-s recovery period in which they must jog from cone B towards cone A, and then back to cone B before the commencement of the next shuttle. In this test, the participants are only allowed two consecutive failed attempts before they are withdrawn from the test. That being, if the individual fails to reach cone C and back to cone B in the allocated time, one fail is issued. If this happens a second consecutive time, then they are eliminated. Once withdrawn from the test, the individual’s score must be recorded. The YYIR1 typically lasts for 5–15 min [28]. The test is comprised of 91 shuttles and can last up to approximately 29 min; however, it is very unlikely somebody will complete it. Scores can be presented in three ways: (1) total distance (meters), (2) level achieved, or (3) VO2 max. Total distance is more simple to understand and calculate, whereas level achieved is more complex as the test begins at level 5 and then skips to level 9 at the beginning.

### Plans to promote participant retention and complete follow-up {18b}

After confirming the commitment of the participants and obtaining papers proving their consent to participate, the responsible researcher will send reminders to attend their sessions through text messages, WhatsApp messages, and phone calls. All the participants can contact the intervention coordinator and the responsible researcher 24 h a day by calling their cell phones.

### Data management {19}

Data will be stored in the Departments of Radiology and Physical Therapy at Tishreen University Hospital with a password-protected computer file, to which only researchers will have access. Throughout the duration of the research study, the file password will be changed once a month. The first author will have a backup copy of all the information.

### Confidentiality {27}

Files with participant’s information will be coded with individual identification codes.

### Plans for collection, laboratory evaluation, and storage of biological specimens for genetic or molecular analysis in this trial/future use {33}

The trial does not involve any genetic or molecular analysis of biological specimens derived from humans. Our muscle measurements will be done in the Radiology Department and Physical Therapy Department at Tishreen University Hospital, and the data will be stored in a protected file on secure computer in the Hospital. Files with participant’s information will be coded with individual identification codes.

## Statistical methods

### Statistical methods for primary and secondary outcomes {20a}

We will use the SPSS V20 for statistical data analysis. First of all, we will calculate “mean separation” as a comparison for every means. The objective is to identify where and how many differences exist. Normality tests (SPSS Explore) will be used to determine if the data is well modeled by a normal distribution, and to compute how likely it is for a random variable. Paired samples *t* test will be used to compare the mean of every group to measure the effects of every single training method. Independent samples *t* test will be used to compare the mean between the football and aerobic groups before and after the intervention.

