**Methods:**

The study sample consists of 60 untrained but healthy men (50–60 years old), who will be randomly assigned (strata: age, activate) to two groups: football group (*n* = 30) and aerobic group (*n* = 30). The intervention will take place within 12 consecutive weeks, two times a week for 60 min each session. The football group will perform recreational football training as a large-sided game, whereas the aerobic group undergoes a running exercise. Both groups have the same external workload ranging between moderate and high exercise intensity. The outcome measure will be collected before and after the intervention period.

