### Objectives {7}

The main objective of this randomized controlled trial is to determine the effects of football versus traditional aerobic exercise training on muscle architecture, such as MT, ML, fascicle length (FL), PA, PT length, thigh muscle power, work, and torque. A secondary objective is to examine the effects of both training programs on aerobic capacity and explosive power.

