In the main part of the training, we will focus on small game running (20–30–40 m) × 5–10 with 3–5 sets and 1–2 min rest between sets for (AG). Also in the same training load, FG will perform competitive activities like small- or large-sided game or a football match (4 vs 4, 5 vs 5, etc.). All participants in both groups will work in the same/similar conditions and rules. None of the participants will play as a goalkeeper in the FG (Table 2). The level of effort for muscle-strengthening activities should be between moderate and high. On a 10-point scale, where no movement is 0, and maximal effort of a muscle group is 10, the moderate-intensity effort is a 5 or 6 and high-intensity effort is a 7 or 8 (the ACSM guideline recommendations have been considered) Table 2.

**Table 2 Tab2:** Exemplary training programs for the aerobic and football group

Training time	FG	AG	Intensity
5 min	Warm-up	Warm-up	Low
15 min	Injury prevention (FIFA11 ± functional training)	Injury prevention (FIFA11 ± functional training)	Moderate
35 min	Football match (competition activities)	Aerobic training (running)	Moderate to high
5 min	Cooldown	Cooldown	Low

Football players practice small-sided games (3 vs 3, 4 vs 4, 5 vs 5, 6 vs 6) with the average heart rate of 155 to 167 bpm [12]. The intensity of small- or large-sided game is moderate and high (the percentage of HRMAX is between 70 and 85%). Both groups will have the same session load (Table 3).

**Table 3 Tab3:** Training session volume and load

	Time	Sets	Rep	Rest	Effort point scale
Warm-up	5 min				3–4
Injury prevention	15 min	2–4	4–8	40 s	4–5
Main part	35 min	3–5	5–10	1–2 min	7–10
Cooling	5 min	–	–	–	1–2

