### Sample size {14}

The sample size was calculated by using “Gpower” software 3.1.9.2. For the determination of the effect size, we made a pilot study which included 10 participants from every single group. We measured the PA of VM for both groups. The mean (M) for football group was 10.59 and 8.17 for AG. Also, the standard deviation (SD) for FG was 2.80 and 2.01 for aerobic one. Based on this, the effect size was 0.992. The α level was 0.05, and the power was 0.95. The minimum numbers of sample were 46 participants.

We raise the sample to 60 for better result. Sixty untrained but healthy adult men are equally divided into two groups (mean ± SD age 55 ± 5). This sample includes a dropout of 15% and provides a moderately detectable change between a group with an alpha level of *p* < 0.05. Some of them had experienced some of the age-related neuromuscular problems or diseases, at least within the last year.

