### Concealment mechanism {16b}

Allocation concealment will be achieved using sequentially numbered, opaque sealed envelopes [17]. Participants will be assigned in two intervention groups: a football group and aerobic group in a 1:1 ratio. Allocation concealment will be ensured. The randomization code will not release until the participants have been recruited into the trial, which takes place after all baseline measurements have been completed.

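### The between-arm t test at follow-up leaves out the baseline value of the outcome, which costs precision, and the within-arm paired t tests cannot be read as programme effects

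*Protocol article*

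**What the plan says.** The main objective is to "determine the effects of football versus traditional aerobic exercise training on muscle architecture" (Objectives {7}), which is a contrast between two randomised arms. The trial allocates men to "a football group and aerobic group in a 1:1 ratio" (Concealment mechanism {16b}); both arms train and there is no untrained arm. On measurement, the abstract states: "The outcome measure will be collected before and after the intervention period". Table 4 likewise schedules assessments at baseline and at follow-up.

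The section on statistical methods {20a} names two inferential tests:

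- An independent-samples t test that "will be used to compare the mean between the football and aerobic groups before and after the intervention".
- A paired t test that "will be used to compare the mean of every group to measure the effects of every single training method".

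On a plain reading, the first is one test between arms at baseline and another at follow-up. The article states no baseline covariate, no comparison of change scores between arms and no group-by-time term.

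The abstract says that participants are "randomly assigned (strata: age, activate"). Sequence generation {16a} describes permuted blocks of four and six and mentions no strata.

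**The concern.** The method is stated, so this is not a detail left to a later analysis plan. It raises two problems.

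**Between arms.** A participant's baseline value is usually a good predictor of his value 12 weeks later. A test on post values alone leaves that variation in the error term. A chance difference between the arms at baseline also stays in the point estimate. Testing the arms against each other at baseline does not help: under randomisation any difference there is due to chance, and the test adjusts nothing. At stake is power for differences smaller than the one seen in the pilot. The Discussion expects differences of moderate size only.

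**Within arms.** The paired tests are given the task of measuring each programme's effect. Without an untrained arm, a before-to-after change combines training with familiarity with the tests and the passage of time. Nor does either paired test address football versus running.

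**Working it through.** **Inputs from the protocol article (Sample size {14})**

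- Pilot pennation angle of vastus medialis: means 10.59 and 8.17, SDs 2.80 and 2.01, stated effect size 0.992.
- "The α level was 0.05, and the power was 0.95". The stated minimum is 46 and the planned total is 60.
- Dropout of 15%: 60 × 0.85 = 51 completers, taken as 26 + 25.

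**Assumptions, not in the protocol**

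- Baseline-to-post correlation r from 0.3 to 0.9.
- A moderate difference taken as 0.5 SD.
- Two-sided alpha of 0.05.

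**Step 1. Reproduce the plan's own figure.** Pooled SD = sqrt((2.80² + 2.01²)/2) = 2.437. Effect size = (10.59 - 8.17)/2.437 = 0.993, against 0.992 stated. An unadjusted two-sample t test (noncentral t) with 23 per arm and one-sided alpha 0.05 has power 0.952, so 46 is reproduced. A two-sided test would need 28 per arm, 56 in total. The article does not state sidedness; that is a separate matter. What counts here is that the sample size also rests on an unadjusted comparison of two means.

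**Step 2. Precision.** The ratio of the ANCOVA standard error to the post-only one is sqrt(1 - r²). For r = 0.7: sqrt(1 - 0.49) = 0.71.

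**Step 3. Power for 0.5 SD with 51 completers.** The post-only noncentrality is 0.5 × sqrt(26 × 25/51) = 0.5 × 3.570 = 1.785 on 49 degrees of freedom, giving power 0.42. ANCOVA divides the noncentrality by sqrt(1 - r²). For r = 0.7 this is 1.785/0.714 = 2.50, giving power 0.69. The degrees of freedom spent on covariates change these figures by about 0.001.

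| Assumed r | SE ratio | Power, post-only | Power, ANCOVA |
|---|---|---|---|
| 0.3 | 0.95 | 0.42 | 0.45 |
| 0.5 | 0.87 | 0.42 | 0.52 |
| 0.7 | 0.71 | 0.42 | 0.69 |
| 0.8 | 0.60 | 0.42 | 0.83 |
| 0.9 | 0.44 | 0.42 | 0.98 |

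**Step 4. Power at the plan's own effect.** With an effect of 0.992 the post-only two-sided test has power 0.93 with 51 completers and 0.97 with all 60.

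**Step 5. Validity.** In a simulation (20,000 replicates, 30 per arm, no true difference between arms) the post-only test rejected in about 5% of trials. The fault is lost precision, not bias or false positives.

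**Step 6. What two paired tests can show.** In the same simulation, with r = 0.7 and the same true change in both arms, one arm was significant and the other not in 40%, 50% and 34% of trials, for true changes of 0.2, 0.3 and 0.4 SD. Two within-arm p values set side by side therefore say little about a difference between programmes.

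**The case against.** The strongest reply is that a post-only t test in a randomised trial is a legitimate analysis. Its standard error already allows for chance baseline imbalance, and at the effect used for planning it has ample power. All of that stands. It means that the point concerns efficiency and that the planned test does not give a wrong answer.

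The gain also depends on an unknown r. At r = 0.3 it is slight (0.42 to 0.45). The ultrasound ICCs cited in the article (0.92 to 0.999 for muscle size) might tempt a reader to treat r = 0.9 as typical. They describe measurement reliability, not correlation across 12 weeks of training, and they do not cover the dynamometer, jump or Yo-Yo outcomes.

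Four stronger readings are not supported:

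- **That the plan ignores baseline altogether.** The paired tests use each man's baseline; only the between-arm comparison leaves it out.
- **That the plan infers a programme difference from one significant and one non-significant paired test.** It does not propose this; it specifies a separate test between arms. Step 6 shows a hazard for readers, not a stated rule.
- **That the shared block in Table 2, "Injury prevention (FIFA11 ± functional training"), confounds the comparison.** It is the same 15 minutes in both arms, so it does not confound football versus running. If a training method means the whole session, the block is part of that method.
- **That the analysis omits known stratification factors.** The strata appear only in the abstract, the second one is unclear, and Sequence generation {16a} has none. Whether randomisation was stratified is unresolved.

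The lack of an untrained arm is a feature of an active-comparator design and no fault in itself. What remains is that the paired tests are given a purpose which that design cannot serve.

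**Conclusion.** The concern holds as a recommended improvement at no cost in data; it does not show the planned analysis to be invalid. The between-arm test omits a baseline value that is already collected. For an assumed difference of 0.5 SD and 51 completers, adjusting for it would raise power from 0.42 to between 0.45 and 0.98 as r goes from 0.3 to 0.9. Both r and the 0.5 SD are assumptions: the protocol gives no correlation and does not quantify the moderate differences that it expects. If the true effect is near 0.992, little power is at stake.

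Separately, the stated purpose of the paired tests is not supported. Change within one arm cannot be attributed to that programme alone, and it does not answer the main objective.

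**What to change.** 1. Make the primary between-arm analysis of each outcome an ANCOVA of the post-intervention value on arm and the baseline value of the same outcome. Report the adjusted mean difference with its 95% confidence interval.
2. Reconcile the abstract with Sequence generation {16a} on stratification. If randomisation was in fact stratified, add the factors actually used as covariates; if not, correct the abstract.
3. Report within-arm changes as means with confidence intervals, and remove the statement that they measure each programme's effect.
4. Replace the baseline t test with descriptive baseline statistics by arm. The test does no harm unless it is used to choose the analysis, but it tells the reader nothing useful.

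The cost is a revision of the statistical methods text, best settled before the data are analysed. No further measurements or participants are needed, because baseline is already scheduled for every outcome.

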### Interim analyses {21b}

This is not applicable.

### Methods for additional analyses (e.g., subgroup analyses) {20b}

The statistical analysis is performed by an independent statistician, blinded for the group allocation by the end of the retest procedure. Perhaps there will be none, the group is not large but perhaps you are looking at differences based on area men live, if they previously played team football, etc.

### Methods in analysis to handle protocol non-adherence and any statistical methods to handle missing data {20c}

#### Regression imputation [24]

Imputation is the process of replacing the missing data with estimated values. Instead of deleting any case that has any missing value, this approach preserves all cases by replacing the missing data with a probable value estimated by other available information. After all missing values have been replaced by this approach, the dataset is analyzed using the standard techniques for a complete data.

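### Single regression imputation followed by ordinary t tests treats imputed values as observed: with arm in the imputation model the between-arm error rate exceeds 5%, with arm left out the effect is attenuated, and the paired tests are too liberal either way

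*Protocol article*

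**What the plan says.** The section on non-adherence and missing data {20c} names one method, regression imputation. It says that "this approach preserves all cases by replacing the missing data with a probable value estimated by other available information", and then: "After all missing values have been replaced by this approach, the dataset is analyzed using the standard techniques for a complete data". It mentions no repeated imputation, pooling or variance correction, and does not say which variables enter the regression.

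The complete-data techniques are given in the statistical methods section {20a}. Between arms: "Independent samples *t* test will be used to compare the mean between the football and aerobic groups before and after the intervention". Within arms: "Paired samples *t* test will be used to compare the mean of every group to measure the effects of every single training method".

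The sample size section {14} plans 60 men, 30 per arm, and allows for loss: "This sample includes a dropout of 15" per cent. The planning values are "Based on this, the effect size was 0.992" and "The α level was 0.05, and the power was 0.95".

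**The concern.** This is not detail left to a separate analysis plan. The article chooses a method and says how the completed data will be analysed.

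A regression prediction lies on the fitted line. Filling in predictions removes the residual scatter that the missing men would have shown, so the sample variance falls. The t test also counts those men in the sample size and the degrees of freedom. Both effects make the reported standard error too small when the imputation preserves the arm difference.

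Whether it does so depends on the regression. Without arm as a predictor, missing men in both arms are filled in from one common line, which pulls the arms together. The first case risks false positives in the main comparison, the second an understated effect. Every outcome with missing post values would be handled in the same way.

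**Working it through.** **Inputs from the article.** 30 men per arm; 15% dropout, so 0.15 × 60 = 9 missing post values (taken as 4 in one arm and 5 in the other); α = 0.05; planning effect 0.992 SD.

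**The article's own effect size.** "The mean (M) for football group was 10.59 and 8.17 for AG", with SDs 2.80 and 2.01. Pooled SD = √((2.80² + 2.01²)/2) = 2.437, so d = (10.59 − 8.17)/2.437 = 0.993, which agrees with the stated 0.992. This value serves as the true effect in step 4.

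**Assumptions.** The correlation r between baseline and post value is not in the article, so a range from 0 to 0.9 is shown. Post values are normal with unit variance and missing completely at random. Tests are two-sided at 0.05.

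**Step 1: the mechanism by hand, r = 0, arm in the model.** Each missing man effectively receives his arm's observed mean.
- True standard error, from 26 and 25 observed men: √(1/26 + 1/25) = 0.280.
- Variances after imputation: 25/29 and 24/29 of the true value, because the imputed men add degrees of freedom but no scatter.
- Reported standard error: √((25/29 + 24/29)/30) = 0.237.
- Ratio: 0.237/0.280 = 0.85, so the reported value is about 15% too small.

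**Step 2: simulation, arm in the model, 15% missing, no true difference.**

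| r | Reported SE | True SE | Ratio | Type I error, arm as covariate | Type I error, imputed by arm |
|---|---|---|---|---|---|
| 0 | 0.238 | 0.279 | 0.85 | 9.5% | 9.8% |
| 0.3 | 0.240 | 0.279 | 0.86 | 9.2% | 9.2% |
| 0.5 | 0.243 | 0.275 | 0.88 | 8.4% | 8.4% |
| 0.7 | 0.248 | 0.269 | 0.92 | 7.1% | 7.2% |
| 0.9 | 0.255 | 0.263 | 0.97 | 5.6% | 6.0% |

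The SE and ratio columns are for arm as a covariate.

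Cross-check at r = 0.5: the critical value on 58 degrees of freedom is 2.002. A standard error that is too small by the factor 0.885 makes the effective cut-off 2.002 × 0.885 = 1.77, and the two-sided tail beyond 1.77 is 8.2%, in line with the simulated 8.4%.

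A further simulation gave 10.1% (r = 0), 8.5% (r = 0.5), 6.3% (r = 0.8) and 6.0% (r = 0.9).

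**Step 3: a random residual added to the single imputation.** The error is still 6.1% to 7.8% for r = 0.9 down to 0.3, so this variant is no cure.

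**Step 4: arm left out of the model.** Under no true difference, the between-arm test runs at 4.8% to 5.2%. Under a true difference of 0.992 SD, the imputed men sit near the common mean. Expected estimate: 0.992 × (25 + 25/51)/30 = 0.992 × 0.85 = 0.843. The simulated mean is about 0.85. The loss is about 14–15% of the effect.

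**Step 5: within-group paired t tests.** In the arm with 4 missing values the error is 6.7–8.3% with arm in the model and 6.4–7.3% without. Across all runs, including the arm with 5 missing, the range is about 6–10%.

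**Step 6: alternatives on the same data.** The t test on observed cases holds 5.0–5.2%. Multiple imputation with arm and baseline in the model and Rubin's rules holds 4.5–4.7% (r = 0.3 to 0.9). The fault therefore lies in the imputation method and not in the missingness as such.

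**The case against.** **The inflation is not universal.** A reader might infer that every interval is too narrow and that every test exceeds 5%. The article does not support this, because it does not say whether arm enters the regression. If it does not, the between-arm test keeps its level and the error runs in the conservative direction. This stands, and the point is stated conditionally for that reason.

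**The size rests on an assumed r.** The upper end, near 10%, needs a baseline value that says nothing about the same man's post value. The article has the same examiner measure the same site and limb, and cites ultrasound reliability of 0.91 to 0.999. These are reliability figures, not correlations across 12 weeks of training, but they make the milder end more plausible for the ultrasound outcomes: about 6% at r = 0.9 and 7% at r = 0.7. This stands as a limit on size.

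**The 15% is an allowance, not an observed rate.** With 5% missing the between-arm error is only 5.3–6.5%. The discontinuation section {11b} also says that men who are injured or cannot follow the sessions are excluded. If that means exclusion from the analysis, fewer values would be left to impute; it may equally mean leaving the training only. The article does not settle this, so the results apply at the article's own allowance.

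None of these objections makes the stated method sound. Under either imputation model at least one planned analysis is damaged.

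**Conclusion.** The concern holds in conditional form. At 15% missing post values:
- **Arm in the model, or imputation by arm:** between-arm type I error about 6% to 10% (r = 0.9 down to 0), with the standard error about 12% too small at r = 0.5.
- **Arm left out:** between-arm error near 5%, but a true 0.992 SD difference is estimated at about 0.84–0.85 SD.
- **Paired tests within arms:** about 6–10% in either case.

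These figures assume normal outcomes, values missing completely at random, two-sided tests and the stated range for r. The mechanism is certain; the exact size is not, because r, the imputation model and the eventual amount missing are not known from the article.

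**What to change.** Remove single regression imputation from section {20c} and state one or both of the following:

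- Analyse all randomised men with an observed post value, preferably adjusted for baseline. The adjusted analysis is valid if missingness depends only on baseline and arm.
- Use multiple imputation with arm and baseline in the imputation model, combined by Rubin's rules.

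Add a sensitivity analysis for departures from missing at random, for example by shifting the imputed values in one arm. State whether men excluded under {11b} are still measured at the post-test and kept in the analysis.

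Baseline adjustment is preferable but not needed to cure this fault, since the t test on observed cases already holds its level in the simulation. The change needs no new data, visits or participants. It costs revised wording, a little more analysis work and slightly wider intervals. It should be made before the data are analysed, so that the imputation model is not chosen with the results in view.
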